#### VR Sham

Participants randomized to the sham group will undergo an 8-week VR sham (3 times per week, 10-min sessions) in addition to the NTR program. Participants in the sham group will be able to select and immerse themselves in VR environments (eg, beach and forest) using a medical-grade, wireless system (Limbix Health, Inc). However, participants in the sham group will not participate in any guided mindfulness meditation or mindful movement activities. While the sham environment may promote relaxation, these participants will not learn the mindfulness skills and techniques cultivated through the Headspace XR activities. Therefore, this group will receive an appropriately designed sham intervention by mimicking the experimental intervention as closely as possible, excluding only the active therapeutic element. It is hypothesized that without exposure to specific mindfulness tools, participants in the sham group will exhibit higher levels of injury-related fear and worse jump-landing biomechanics at the end of the study compared to the intervention group. Each VR sham session is 10 minutes in length.

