#### The VRMM Intervention

Participants randomized to the intervention group will undergo an 8-week VRMM intervention (3 times per week, 10-min sessions) in addition to the NTR program. VRMM engages visual and auditory senses to enhance the mindfulness experience and has been successfully used to address chronic pain [38] and anxiety [28,39]. The VRMM intervention will be administered with a commercially available wireless headset (MetaQuest, Meta Platform, Inc) using the Headspace XR application (Headspace, Inc). Prior to the first VRMM session, participants randomized into the VRMM+NTR group will watch a 10-minute educational video on the VR headset detailing the benefits of mindfulness. This will allow the participant to also gain exposure to the feel of the VR headset prior to the implementation of the intervention.

Participants enrolled in the VRMM group will complete a guided mindfulness experience that encourages observation, acceptance, and being present in their current environment through breath awareness. Participants will have the opportunity to complete a variety of mindfulness activities through the Headspace XR application, including focused attention mindfulness (eg, meditation and breath control) and mindful movement. While not directly associated with knee-specific activity, mindfulness was selected because individuals after ACLR must learn how to acknowledge their feelings while maintaining relaxation in specific environmental situations, rather than avoiding stressful situations or difficult emotions. Participants will also engage in mindful movement while in the headset to encourage mindfulness during the integration of movement. Engaging in mindfulness can be beneficial for retraining attentional control systems.

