Mood stream	Players select daily mood and reflect on that emotion.
Body scan	A foundational full-body scan to notice sensations and reduce stress.
Focus slingshot	Players pay attention to timing to release the slingshot and paint a wall.
Take a beat meditation	Meditation based on selected mood.
Box breathing	Inhale 4 s, hold 4 s, exhale 4 s, hold 4 s guided by a visual.
Energy boost	Players collect orbs and stars through full-body movement.
Kindness bubbles	Players grab hearts representing positive feelings and pop bubbles to release negative ones.
Focus hoops	Players follow flashing hoops in sequence and shoot accordingly.
Backward counting	Players count backward while gently noticing distraction.
Breathing slingshot	Slingshot release timed with inhale and exhale.

The active ingredient of this intervention for participants is learning specific mindfulness skills and tools including focused attention, present-moment awareness, breathing skills, and mindful movement. It is hypothesized that these skills will provide participants with tools to overcome fearful situations, resulting in lower injury-related fear and improved jump-landing biomechanics following the intervention compared to the sham group.

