**Figure 2. F2:**
[figure not shown]
CONSORT (Consolidated Standards of Reporting Trials) participant flow diagram. NTR: neuromuscular training rehabilitation; VRMM: virtual reality mindfulness meditation.

Adherence to the VRMM and NTR components of interventions will be tracked by study interventionists. We expect moderate adherence (attending 50%‐75% of sessions) to high adherence (attending >75%) of sessions in 75% of participants throughout the 8-week trial. The type and number of mindfulness meditation sessions and the number of sets/reps of each exercise within the NTR program will be documented, along with any relevant notes about the sessions.

Acceptability will be assessed with a 6-item questionnaire that asks participants about the perceived helpfulness, benefits, and tolerability of both the VR and rehabilitation sessions (Table 5). Questions will be answered on a 0- to 100-point sliding visual analog scale with anchoring labels at 0, 50, and 100 (Table 4). The acceptability survey was adapted from previous works testing psychological interventions for patients following ACLR [40,41]. Participants in both the intervention and sham groups will answer the acceptability survey as both groups will be exposed to the NTR and VR headset in some capacity. We hypothesize that participants in the VRMM+NTR group will exhibit higher acceptability scores than those in the VRMM sham+NTR group.

**Table 5. T5:** Acceptability questionnaire for participants, completed at the trial post assessment.

Question	Response anchors on visual analog scale
How helpful was the virtual reality?	Not helpful (0) Helpful (50) Most helpful (100)
How likely are you to recommend virtual reality to a friend?	Not likely (0) Likely (50) Most likely (100)
Please rate the benefit-to-effort relationship of the virtual reality.	The effort far outweighed the benefits (0) The effort equaled the benefits (50) The benefits far outweighed the effort (100)
How much did your fear change during the virtual reality?	Fear decreased a meaningful amount (0) Fear did not change (50) Fear increased a meaningful amount (100)
How tolerable was the virtual reality headset?	Not enjoyable (0) Neutral (50) Enjoyable (100)
How tolerable were the rehabilitation sessions?	Not enjoyable (0) Neutral (50) Enjoyable (100)

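### The sham is said to remove only the active element, but headset, software, choice of content and an educational video also differ, so superiority and higher acceptability belong to the package, not to mindfulness skills alone

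*Protocol article*

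**What the plan says.** The VR Sham section describes the control as "mimicking the experimental intervention as closely as possible, excluding only the active therapeutic element". The section on the VRMM intervention defines that element, below Table 4, as "learning specific mindfulness skills and tools including focused attention, present-moment awareness, breathing skills, and mindful movement".

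The hardware is described separately for each arm. VRMM is given on a "commercially available wireless headset (MetaQuest, Meta Platform, Inc) using the Headspace XR application (Headspace, Inc"). The sham is given "using a medical-grade, wireless system (Limbix Health, Inc"). Sham participants "will be able to select and immerse themselves in VR environments (eg, beach and forest"), whereas VRMM participants follow one fixed-order sequence of activities (text above Table 3).

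Under Outcomes, Feasibility (Aim 1), the article sets a between-arm expectation: "We hypothesize that participants in the VRMM+NTR group will exhibit higher acceptability scores than those in the VRMM sham+NTR group". The Discussion (Rationale and Principal Findings) expects better results in those exposed to the active ingredients. It makes a larger trial depend on the hypotheses for recruitment, retention, adherence and acceptability being supported, together with promising preliminary efficacy.

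**The concern.** A sham that removes one element and nothing else lets a difference between arms be read as the effect of that element. The word *only* claims this property. If the arms also differ in things outside the declared element, the trial still compares two packages without bias from allocation, but it cannot say which part of the package made the difference.

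Two conclusions are at stake. The first is efficacy: the Discussion plans to credit superiority to the mindfulness ingredients, and that reading would carry into the case for the next-stage trial. The second is acceptability. The two arms would be scoring different devices and different software, so a higher or lower VRMM score could reflect the equipment. In a trial whose primary purpose is feasibility, an equipment difference could then support or defeat a hypothesis on which progression depends.

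**Working it through.** The question is whether each described difference between the arms lies inside or outside the declared active ingredient. No power or sample size figure enters.

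**VR time.** Each of the six session templates in Table 3 adds to the stated 10 minutes: 1+5+2+2 in four of them and 1+2+5+2 in two. Three sessions a week for 8 weeks give 10 × 3 × 8 = 240 minutes. The sham has the same session length and frequency.

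**The differences, side by side.**

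| Feature | VRMM arm | Sham arm | Part of the declared ingredient? |
|---|---|---|---|
| Headset and software | MetaQuest with Headspace XR | Limbix system | No; differs for all 240 minutes |
| Choice of content | Fixed-order programme | Participant selects the scene | No |
| Introductory video on mindfulness | 10 minutes, also serves as headset familiarisation | None described | No |
| Guided meditation and breathing | Yes | No | Yes |
| Play activities (labelled mindful movement in Table 3) | Yes | No | Yes |
| Use of a VR headset, session length, frequency, NTR | Yes | Yes | Matched |

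The first three rows are enough to contradict *only*.

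**Play and movement.** Play takes 2+5+2 = 9 minutes in odd weeks and 2+2+5 = 9 in even weeks, so 9 × 8 = 72 of 240 minutes (30%). Reflect takes 3 × 24 = 72 minutes and Unwind 12 × 8 = 96, and 72 + 96 + 72 = 240. Within Play, Energy boost ("Players collect orbs and stars through full-body movement") takes 5 × 8 = 40 minutes (40/240 = 16.7%). These minutes are mostly intended contrast, because the definition of the ingredient includes mindful movement and the VR Sham section says openly that the sham omits it. They show only that game play and physical movement come bundled with attention and breathing skills, and that two arms cannot separate them.

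**Acceptability.** Of the six items in Table 5, one rates the headset, four ask about the virtual reality (helpfulness, recommendation, benefit against effort, change in fear) and one asks about the rehabilitation sessions. So five of six items refer to something that differs in hardware and software between arms. The between-arm expectation is the only acceptability statement in the Outcomes section worded as a hypothesis, and the Discussion ties progression to the acceptability hypotheses. The Statistical Analysis section already gives absolute thresholds: 50% for moderate and 80% for high acceptability.

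**The case against.** The strongest reply is that the article treats VRMM as a multi-component package. Its definition of the active ingredient, the labels in Table 3 and the Discussion all include mindful movement, and separating components is not an aim. VR is presented as the means of delivery, so the headset is fairly part of what participants judge. Acceptability is listed for descriptive statistics, with thresholds already set, and is not among the ANOVA outcomes. VRMM participants also have some choice, since they select a daily mood that shapes one meditation. The article further says that no firm conclusions on effectiveness will be drawn.

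Much of this stands, and it rules out several stronger readings that a reader might infer:

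- *That the 72 Play minutes contradict the sham claim.* They fall within the element that the sham is meant to exclude.
- *That movement in VR biases the landing outcomes.* Five minutes a week of Energy boost sits beside a three-times-weekly NTR programme with bounding, jumps and hops in both arms. The documents give no basis for such an effect.
- *That the relaxing sham is an error.* The article discloses that the scenes may relax participants and explains that no skills are taught.
- *That the randomized comparison is invalid.* It remains a valid comparison of the two packages.

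The reply does not reach the headset and software, the fixed against self-selected content (the mood choice narrows this but leaves the programme set), or the video. It also leaves in place a between-arm acceptability hypothesis linked to progression. Nor does this rest on detail that the article left to a fuller document: it concerns an affirmative statement contradicted by other statements in the same article.

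**Conclusion.** The concern holds in a limited form. The sham does not have the property claimed for it, because three described differences lie outside the declared active ingredient and one of them, the device and its software, covers all 240 VR minutes. Any superiority can be credited to the Headspace XR package as delivered, with its headset and introductory video, but not to mindfulness skills alone. The between-arm acceptability comparison mixes the content with the equipment in five of six items and should not decide progression.

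The size of any device, choice or expectancy effect cannot be derived from the documents, and none is asserted. The video could raise expectations on a self-reported fear score, but that is a possibility and not a demonstrated bias. The conclusion assumes that the sham arm receives no comparable introductory video, as the article's description implies.

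**What to change.** 1. In the VR Sham section, remove *only*. State that the contrast is the Headspace XR package, as delivered on its headset and with its educational video, against self-selected VR scenes on another device.
2. In the Discussion, credit any superiority to that package. Say that game play and movement cannot be separated from the other mindfulness components.
3. Drop the between-arm acceptability hypothesis as a progression criterion, at least for the items on the headset or the virtual reality. Base the acceptability part of the progression decision on VRMM-arm scores against the existing 50% and 80% thresholds, and report sham scores descriptively. The fear-change item is anchored so that a low score is favourable, so reverse it or report it apart before applying a threshold.

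The cost is wording and reporting; the downside is a narrower conclusion. The sham device should not be changed as part of this fix. With 12 of 48 randomized, and assuming an even 1:1 split so far, about 6 of the 24 sham participants would have used one device and about 18 another. Device would then be confounded with calendar time, and the documents do not show that a suitable scene application exists for the VRMM headset.

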### Treatment Fidelity

To ensure treatment fidelity, all interventionists will follow standard operating procedures that detail the VRMM+NTR procedures and the VR sham+NTR procedures, including the frequency, intensity, and duration of all activities. Additionally, prior to working with participants, all interventionists will undergo training to ensure that they are safely and effectively implementing the intervention and sham. Throughout the intervention, all interventionists will complete an adherence checklist to describe completed activities during each session. Finally, quality control checks will occur to identify issues as they arise and to maintain consistency of the intervention/sham delivery over time.

### Outcomes

#### Feasibility (Aim 1)

Recruitment and retention (ie, screening, enrollment, consent, randomization, intervention/sham completion, and study completion) will be documented throughout the trial (Figure 2). Monthly recruitment rates will be calculated as the number of recruited and consented participants divided by the number of eligible participants (ie, those screened into the study). Regular enrollment reports outlining this information are being sent to the federal agency monthly. The goal recruitment rate is 1 to 3 participants per month over a 45-month timeframe (September 2023 to May 2027). Retention will be calculated as the percentage of participants retained during the 8-week period, and all reasons for dropout will be documented. We expect that more than 75% of participants will be retained during the 8-week period for both VRMM+NTR and VR sham+NTR groups.

**Figure 2. F2:**
[figure not shown]
CONSORT (Consolidated Standards of Reporting Trials) participant flow diagram. NTR: neuromuscular training rehabilitation; VRMM: virtual reality mindfulness meditation.

Adherence to the VRMM and NTR components of interventions will be tracked by study interventionists. We expect moderate adherence (attending 50%‐75% of sessions) to high adherence (attending >75%) of sessions in 75% of participants throughout the 8-week trial. The type and number of mindfulness meditation sessions and the number of sets/reps of each exercise within the NTR program will be documented, along with any relevant notes about the sessions.

Acceptability will be assessed with a 6-item questionnaire that asks participants about the perceived helpfulness, benefits, and tolerability of both the VR and rehabilitation sessions (Table 5). Questions will be answered on a 0- to 100-point sliding visual analog scale with anchoring labels at 0, 50, and 100 (Table 4). The acceptability survey was adapted from previous works testing psychological interventions for patients following ACLR [40,41]. Participants in both the intervention and sham groups will answer the acceptability survey as both groups will be exposed to the NTR and VR headset in some capacity. We hypothesize that participants in the VRMM+NTR group will exhibit higher acceptability scores than those in the VRMM sham+NTR group.

**Table 5. T5:** Acceptability questionnaire for participants, completed at the trial post assessment.

Question	Response anchors on visual analog scale
How helpful was the virtual reality?	Not helpful (0) Helpful (50) Most helpful (100)
How likely are you to recommend virtual reality to a friend?	Not likely (0) Likely (50) Most likely (100)
Please rate the benefit-to-effort relationship of the virtual reality.	The effort far outweighed the benefits (0) The effort equaled the benefits (50) The benefits far outweighed the effort (100)
How much did your fear change during the virtual reality?	Fear decreased a meaningful amount (0) Fear did not change (50) Fear increased a meaningful amount (100)
How tolerable was the virtual reality headset?	Not enjoyable (0) Neutral (50) Enjoyable (100)
How tolerable were the rehabilitation sessions?	Not enjoyable (0) Neutral (50) Enjoyable (100)

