### Statistical Analysis

Descriptive statistics (means, SD, frequency, and ranges) will be calculated for recruitment, retention rates, adherence, and acceptability outcomes. A threshold of 75% or better will be used as the minimum threshold for acceptable recruitment, adherence, and retention outcomes. A threshold of 50% will represent moderate acceptability, and scores of 80% or better will be used to identify high acceptability [40].

Descriptive statistics will be calculated for participant demographics, TSK-11 scores, peak knee abduction moment, and knee flexion excursion. A 2×2 repeated measures ANOVA will be used to assess changes between the intervention and sham groups. Group and time will serve as our independent variables. The TSK-11 score, peak knee abduction moment, and knee flexion excursion will serve as our dependent variables. The results will be reported as means and mean differences, with 95% CIs, *F*-values (ratio of between-group variance to within-group variance), and *P* values. The significance level will be set at a corrected value of *P*<.02 to reflect multiple comparisons (0.05/3). We hypothesize that patients in the VRMM+NTR group will demonstrate lower injury-related fear, decreased external knee abduction moment, and increased knee flexion excursion when compared to the VR sham+NTR group. Hypotheses for each outcome will be tested independently. We believe that these statistical differences will be supported with moderate to strong effect sizes. Partial η^2^ effect sizes will be calculated to examine the magnitude of the Group × Time interaction. Effect sizes will be interpreted as small if between 0.01 and 0.08, medium if between 0.09 and 0.24, and large if >0.25 [47].

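### The fear-change item in the acceptability survey runs opposite to the other five, but the single 50%/80% rule is stated with no reversal or exemption

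*Protocol article*

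**What the plan says.** The protocol article describes the instrument under Outcomes, Feasibility (Aim 1): "Acceptability will be assessed with a 6-item questionnaire that asks participants about the perceived helpfulness, benefits, and tolerability of both the VR and rehabilitation sessions". On the response format it says: "Questions will be answered on a 0- to 100-point sliding visual analog scale with anchoring labels at 0, 50, and 100".

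Table 5 gives the anchors:

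- Helpfulness of the virtual reality: "Not helpful (0) Helpful (50) Most helpful (100".
- Recommending it to a friend: "Not likely (0) Likely (50) Most likely (100".
- Benefit against effort: "The effort far outweighed the benefits (0) The effort equaled the benefits (50) The benefits far outweighed the effort (100".
- Tolerability of the headset and of the rehabilitation sessions (two items): from not enjoyable at 0, through neutral at 50, to enjoyable at 100.
- Change in fear during the virtual reality: "Fear decreased a meaningful amount (0) Fear did not change (50) Fear increased a meaningful amount (100".

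The Statistical Analysis section gives the only scoring rule for acceptability: "A threshold of 50% will represent moderate acceptability, and scores of 80% or better will be used to identify high acceptability". The between-group expectation stands in the Feasibility section: "participants in the VRMM+NTR group will exhibit higher acceptability scores" than the sham group.

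The Discussion (Rationale and Principal Findings) makes support for the acceptability hypothesis one of the conditions for moving to a larger trial, alongside recruitment, retention, adherence and promising preliminary efficacy.

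**The concern.** Three things are fixed in the text: the direction of each scale, the numerical cut-offs, and the statement that higher acceptability scores are expected with the intervention. For five items they agree. For the fear item they do not, because its high end is the bad outcome. No sentence says that the item is reversed, scored separately or left out of the rule.

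The trial also predicts lower injury-related fear in the mindfulness arm. If the fear item follows that prediction, it moves against the acceptability prediction for the same arm. Acceptability is an Aim 1 outcome, this survey is the only acceptability instrument described, and the result informs whether a larger trial goes ahead.

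**Working it through.** The plan states no figure to reproduce. The check is to apply the printed rule to the printed scale.

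**Inputs.** Six items, each 0 to 100 (Feasibility section). Item direction from Table 5: 100 is favourable on five items and 0 is favourable on the fear item. Cut-offs of 50 and 80 (Statistical Analysis). Let *f* be the response to the fear item and *o* the mean of the other five.

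**Reading 1: thresholds applied per item.**

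| Answer to the fear item | Score as printed | Class | Score reversed (100 − *f*) | Class |
|---|---|---|---|---|
| Meaningful decrease | 0 | below moderate | 100 | high |
| No change | 50 | moderate | 50 | moderate |
| Meaningful increase | 100 | high | 0 | below moderate |

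The classification of this item is fully inverted.

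**Reading 2: unweighted mean of the six items.** This is an assumption; the article defines no total or mean.

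As printed: (5*o* + *f*)/6. With the item reversed: (5*o* + 100 − *f*)/6.

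| *o* | *f* | As printed | Reversed |
|---|---|---|---|
| 100 | 0 | 500/6 = 83.3 | 600/6 = 100 |
| 100 | 100 | 600/6 = 100 | 500/6 = 83.3 |
| 90 | 10 | 460/6 = 76.7 (misses high) | 540/6 = 90.0 (high) |
| 80 | 100 | 500/6 = 83.3 (high) | 400/6 = 66.7 (moderate) |

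The mean that the other five items need to reach 80 as printed is (480 − *f*)/5:

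- *f* = 0: 96
- *f* = 50: 86
- *f* = 100: 76

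To reach 50 it is (300 − *f*)/5: 60 at *f* = 0 and 40 at *f* = 100. Under either cut-off, a participant whose fear fell has to rate everything else higher than one whose fear rose.

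**Effect on the group comparison under Reading 2.** With the other items fixed, a fear response 20 points lower reduces the mean by 20/6 = 3.3 points. Moving from one end of the fear item to the other shifts the mean by 100/6 = 16.7 points, in the wrong direction.

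**The case against.** The strongest reply is that this is silence and not error. The article never says that the fear item is scored unreversed. Coding and combining items is detail that an article often leaves to the full protocol or analysis plan. The survey is described as adapted from earlier work and the thresholds carry a citation, so a scoring rule may exist there. A questionnaire with an item of mixed direction is ordinary design. Part of this stands: a reader might infer that the trial will certainly misclassify participants, and the document does not support that. What remains is that the article does fix anchors, cut-offs and the direction of the hypothesis, and these do not fit together as printed.

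Other stronger readings also go too far:

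- *The better the intervention works on fear, the lower its acceptability score.* This holds only with the other five items fixed. Under the mean, a 20-point larger fall in fear is cancelled by a 4-point gain on each of the other five (5 × 4 = 20), and helpfulness or recommendation could plausibly rise too.
- *A rise in fear by itself makes a participant highly accepting.* This is true of the item under Reading 1. Under Reading 2 the other five must still average 76.
- *The efficacy result on fear is affected.* It is not. Aim 2a uses the TSK-11, and the survey item asks only about change during the virtual reality.
- *The 50% bar is wrong because 50 means neutral or no change on some items.* The bar is a cited convention, and on the helpfulness and recommendation items 50 carries a positive label. A different bar would be a preference. The same goes for reporting the rehabilitation item separately, since the article does not say that the items are pooled.

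It is also fair to say that acceptability is summarised descriptively, that no formal test of it is specified, and that the Discussion gives no acceptability cut-off for proceeding.

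**Conclusion.** The point holds as an inconsistency in the stated scoring. Followed as printed, the rule gives the wrong class at both ends of the fear item if applied per item. If the six items are averaged with equal weight, it caps the best possible experience at 83.3 and can move a participant across the 80% line in either direction. The per-item result needs no assumption beyond applying the rule literally. The figures for the mean rest on the equal-weight assumption, and the between-group effect also rests on the other items being held fixed.

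The weight is moderate. The item bears on an outcome used in the decision to proceed, but it is one of six items and one of several conditions, the raw responses are recoverable, and an analysis plan that is not shown may already handle it.

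**What to change.** Add a scoring statement: the fear-change item is reverse-scored as 100 minus the response before any threshold, summary or group comparison. Alternatively, report it on its own outside the 50%/80% rule. In the same place, state whether the thresholds apply to each item or to a composite and, if to a composite, how it is formed. If the analysis plan already says this, the article's text only needs to be aligned with it.

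The cost is a line or two of text. The questionnaire and the collected responses are unchanged. The article reports 12 of the planned 48 participants randomized and 10 completed, so the rule can be put on record before most of the data exist. That avoids a reversal decided after the scores have been seen.
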